### Evaluation of renal function

Renal function will be evaluated upon enrollment and every year thereafter. For the adult patients, renal function will be measured using the estimated glomerular filtration rate calculated by the Chronic Kidney Disease Epidemiology Collaboration (CKD-EPI) equation [19]. If the patients are in end-stage renal disease or receive renal replacement therapy upon enrollment, renal function will be evaluated retrospectively to calculate the renal function decline rate. For children, renal function will be measured using the estimated glomerular filtration rate calculated by the Schwartz equation [20].

### Imaging analysis

The patients will be classified into typical and atypical cystic kidney disease. Nonenhanced kidney CT will be performed in adult patients. The patients will be encouraged to take water before the CT exams to accurately distinguish the liver and stomach anatomically. All image files from the nonenhanced CT will be retrieved to a workstation and inspected to confirm complete coverage of both kidneys and liver. Images will be reconstructed into 5 mm sections in axial images and 3 mm sections in both coronal and sagittal sections before volume measurements. The total kidney volume will be measured by a professionally educated radiologist. Total kidney volume will be measured by 2 methods: the stereologic method by using semiautomatic volumetry software (ImageJ version 1.5a, https://imagej.nih.gov/ij/) [21] and the manual method by using the Mayo ellipsoid method [18, 22]. Expanded imaging classification will be applied to typical and atypical polycystic kidney cases [23]. The sonographic images and their interpretations will be collected from pediatric patients. The number and distribution of cysts and their characteristics will be reported in our case report form. The radiologist will also measure the muscle area to assess the nutritional status as previously reported [24].

### Genetic pipeline

We will use a stepwise approach to confirm genetic diagnosis. First, we will use a targeted gene panel for the screening method. We designed a targeted gene panel (Twist Bioscience, San Francisco, CA, USA) encompassing 0.5 megabases, including 89 genes related to cystogenesis or ciliopathy as well as genes that are associated with extrarenal phenotypes such as liver cysts (Table 2). Twist technology has provided high-quality target enrichment probes to cover target genes uniformly and efficiently [25]. Targeted exon capture will be performed on genomic DNA samples using a Twist custom panel kit followed by 101 base paired-end sequencing on an Illumina NovaSeq6000 platform (Illumina, San Diego, CA, USA). Sequence reads will be aligned to the human reference genome (GRCh37/hg19) using BWA-MEM and further processed to call single nucleotide variants and indels following the GATK Best Practices workflow [26]. All variants covered by independent sequence reads with a depth of 8x or greater will be annotated with ANNOVAR. All variants will be visualized in silico to eliminate false positives. Additional genetic testing will be performed if the pathogenic mutations were not found using a targeted gene panel or if the patients have severe renal or extrarenal phenotypes compared to other family members. If the patients are clinically classified as having typical ADPKD but pathogenic mutations are not found using a targeted gene panel, the patients will undergo targeted resequencing with long-range polymerase chain reaction (PCR) combined with multiplex ligation-dependent probe amplification (MLPA) to detect large deletions. WES will take place in the following cases: 1) if the patients are clinically classified as typical ADPKD but no pathogenic mutations are found using a previous method, 2) if the patients are clinically classified as atypical polycystic kidney disease or other iCKD but pathogenic mutations are not found using a targeted gene panel, 3) if the patients present with a severe phenotype and variants cannot explain the severity, or 4) if the patients show extremely different phenotypes compared to other family members. Familial segregation analysis will also take place to define the pathogenicity of variants. A schematic representation of the genetic workflow is shown in Fig. 1.

**Table 2 Tab2:** Coverage of cystogenesis-related targeted gene panel

Target gene	Previously reported disease	Coverage
*AHI1*	Joubert syndrome	100%
*ALG8*	Polycystic liver disease	88.61%
*ARL13B*	Joubert syndrome	*98.72%*
*ATF6B*	ER candidate gene (polycystic liver)	100%
*ATXN3*	ER candidate gene (polycystic liver)	97.97%
*AVP*	Polycystic kidney disease	100%
*AVPR2*	Polycystic kidney disease	100%
*C5ORF42*	Joubert syndrome	100%
*CAPN2*	ER candidate gene (polycystic liver)	99.1%
*CC2D2A*	Joubert syndrome	98.13%
*CEP120*	Joubert syndrome	97.02%
*CEP164*	NPHP	100%
*CEP290*	NPHP/MKS	100%
*COL4A1*	Hereditary angiopathy with nephropathy, aneurysms, and muscle cramps	100%
*COL4A3*	Alport syndrome	99.29%
*COL4A4*	Alport syndrome	100%
*COL4A5*	Alport syndrome	100%
*CSPP1*	Joubert syndrome	97.3%
*CYS1*	Cilia-associated cystic genes	100%
*DNAJB11*	Atypical polycystic kidney disease	100%
*DYNC2H1*	Cilia-associated cystic genes	100%
*EDEM3*	ER candidate gene (polycystic liver)	100%
*EYA1*	Branchiootorenal dysplasia syndrome	100%
*FAN1*	Karyomegalic interstitial nephritis	100%
*GANAB*	ADPKD	100%
*GLIS2*	NPHP	100%
*GLIS3*	Neonatal diabetes, hypothyroidism, and cystic kidney disease	100%
*HNF1B*	Renal cysts and diabetes syndrome	100%
*HSP90AA1*	ER candidate gene (polycystic liver)	100%
*HSPA6*	ER candidate gene (polycystic liver)	100%
*HYOU1*	ER candidate gene (polycystic liver)	100%
*IFT140*	Cilia-associated cystic genes	100%
*IFT172*	Cilia-associated cystic genes	100%
*IFT80*	Cilia-associated cystic genes	99.58%
*IFT88*	Cilia-associated cystic genes, phenotype resembling ADPKD	98.7%
*INPP5E*	Joubert syndrome	100%
*INVS*	NPHP	100%
*IQCB1*	NPHP	100%
*KIAA0586*	Joubert syndrome	93.79%
*LRP5*	Polycystic liver disease	100%
*MKS1*	Joubert syndrome/MKS	100%
*MUC1*	ADTKD	100%
*NEK1*	Polycystic kidney disease	100%
*NEK8*	NPHP	100%
*NGLY1*	ER candidate gene (polycystic liver)	100%
*NPHP3*	NPHP	98.29%
*NPHP4*	NPHP	100%
*OFD1*	OFD	100%
*PARK2*	ER candidate gene (polycystic liver)	100%
*PAX2*	Optic nerve coloboma, renal hypoplasia	100%
*PKD1*	ADPKD	100%
*PKD2*	ADPKD	100%
*PKHD1*	ARPKD	100%
*PMM2*	Polycystic kidney disease with hyperinsulinemic hypoglycemia	100%
*PRKCSH*	Polycystic liver disease	100%
*REN*	Familial hyperproreninemia, high blood pressure	100%
*RPGRIP1L*	Joubert syndrome/MKS	96.64%
*SDCCAG8*	NPHP	94.23%
*SEC24B*	ER candidate gene (polycystic liver)	97.43%
*SEC24C*	ER candidate gene (polycystic liver)	100%
*SEC24D*	ER candidate gene (polycystic liver)	100%
*SEC31A*	ER candidate gene (polycystic liver)	97.42%
*SEC31B*	ER candidate gene (polycystic liver)	100%
*SEC61A1*	ER candidate gene (polycystic liver)	100%
*SEC61A2*	ER candidate gene (polycystic liver)	100%
*SEC61B*	Polycystic liver disease	100%
*SEC62*	ER candidate gene (polycystic liver)	100%
*SEC63*	Polycystic liver disease	95.11%
*TCTN2*	Joubert syndrome	100%
*TMEM216*	Joubert syndrome	100%
*TMEM67*	NPHP/Joubert syndrome/MKS	94.94%
*TSC1*	Tuberous sclerosis complex	100%
*TSC2*	Tuberous sclerosis complex	100%
*TTC21B*	NPHP	100%
*TXNDC5*	ER candidate gene (polycystic liver)	95.15%
*UBE4B*	ER candidate gene (polycystic liver)	100%
*UGGT1*	ER candidate gene (polycystic liver)	100%
*UGGT2*	ER candidate gene (polycystic liver)	100%
*UMOD*	ADTKD	100%
*VHL*	Von Hippel–Lindau syndrome	100%
*WDR19*	NPHP	100%
*WDR34*	Cilia-associated cystic genes	100%
*WDR35*	Cilia-associated cystic genes	100%
*WDR60*	Cilia-associated cystic genes	100%
*WFS1*	ER candidate gene (polycystic liver)	100%
*XBP1*	Polycystic kidney and liver diseases	100%

*Abbreviations*: *ADPKD* Autosomal dominant polycystic kidney disease, *ADTKD* Autosomal dominant tubulointerstitial kidney disease, *ARPKD* Autosomal recessive polycystic kidney disease, *ER* Endoplasmic reticulum, mks Meckel syndrome, *NPHP* Nephronophthisis, *OFD* Orofaciodigital syndrome

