### Study participants

A total of 800 participants are planned to be enrolled from May 19, 2019 to May 18, 2022. Patients with ≥3 renal cysts in both kidneys are eligible to be enrolled. Those who are not able to give informed consent or are pregnant will be excluded from enrollment. Cases of simple renal cysts and acquired cystic kidney disease that involve cyst formation as the result of renal failure will also be excluded from this study. However, patients with end-stage kidney disease who are receiving renal replacement therapy due to iCKD can be enrolled.

The patients will be classified into typical ADPKD, atypical polycystic kidney disease, and other iCKDs after enrollment. Typical ADPKD is defined according to Pei-Ravine criteria as previously described [17]. Atypical polycystic kidney disease is defined either when the case is typical ADPKD but the patient does not have a family history of polycystic kidney disease or when the imaging phenotype is atypical as follows: unilateral, asymmetric, segmental, lopsided, bilateral or unilateral atrophic kidneys [18]. Other iCKDs are rare disease entities in children and adolescents. The other iCKDs include but are not limited to the tuberous sclerosis complex, von Hippel-Lindau disease, ADTKD, ARPKD, *HNF-1β*-related disease and NPHP. Among the 800 participants, approximately 650 patients with typical ADPKD, 90 patients with atypical polycystic kidney disease, and 60 patients with other iCKDs will be enrolled.

The parents, siblings, or children of the enrolled patients are recommended to participate in the study by giving whole blood samples for a segregation study. We will collect family samples when genetic diagnosis is undetermined, genotype-phenotype severity is not matched, and when the extrarenal manifestation is severe. We will also collect family samples from the families with more than 3 affected individuals to define gene penetrance and modify gene effects.

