**Fig. 1 Fig1:**
[figure not shown]
Genetic analysis pipeline. A total of 800 probands with iCKD will be enrolled in the study. They will be classified into typical ADPKD, atypical polycystic kidney disease, or other/pediatric iCKDs. For the first screening genetic test, a targeted gene panel of 89 cytogenesis-related genes will be applied to the total population. All the variants will be analyzed by bioinformaticians to identify pathogenic mutations. For those with variants of undetermined significance (VUS) or no variants found by the gene panel, different genetic approaches will be taken for each class of iCKD. For those with typical ADPKD, targeted exome sequencing of *PKD1* after long-range PCR combined with MLPA will be performed to identify pathogenic mutations. If the mutations are not found by this method, WES will take place. For those with atypical polycystic kidney disease or pediatric iCKD, WES will be performed to identify pathogenic mutations. For the last step of genetic diagnosis, a family segregation study will be performed to elucidate the cause of genotype-phenotype discordance, in-family severity discordance, or discordance between renal and extrarenal manifestations. Abbreviations: ADPKD, autosomal dominant polycystic kidney disease; iCKD, inherited cystic kidney disease; PCR, polymerase chain reaction; MLPA, multiplex ligation-dependent probe amplification; PKD, polycystic kidney disease; VUS, variant of undetermined significance; WES, whole exome sequencing

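### The only described large-deletion assay is reserved for panel-negative typical ADPKD; no described step would find large deletions in the other two classes or in non-PKD genes

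*Protocol article*

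**What the plan says.** The Genetic pipeline section sets out a stepwise scheme. Every patient first has the targeted panel, whose reads are "further processed to call single nucleotide variants and indels following the GATK Best Practices workflow". What follows a negative panel depends on the clinical class.

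- **Typical ADPKD.** The condition is "If the patients are clinically classified as having typical ADPKD but pathogenic mutations are not found using a targeted gene panel". These patients have long-range PCR resequencing "combined with multiplex ligation-dependent probe amplification (MLPA) to detect large deletions". The Fig. 1 legend names the gene: "For those with typical ADPKD, targeted exome sequencing of *PKD1* after long-range PCR combined with MLPA will be performed". WES follows if this is also negative.
- **Atypical polycystic kidney disease and other iCKD.** The Genetic pipeline section sends panel-negative patients in these classes directly to WES. The Fig. 1 legend agrees: "For those with atypical polycystic kidney disease or pediatric iCKD, WES will be performed to identify pathogenic mutations". Neither place mentions MLPA or any other dosage step for these classes.

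On relatives, the Genetic pipeline section adds: "Familial segregation analysis will also take place to define the pathogenicity of variants". The Study participants section recommends that relatives give blood and sets the collection triggers: no settled genetic diagnosis, a mismatch between genotype and severity, or severe disease outside the kidney. Families with more than 3 affected members are a further trigger.

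**The concern.** The plan recognises that the panel step can miss large deletions, because it adds an assay for that purpose. It then assigns the assay to one class only. The other-iCKD class includes tuberous sclerosis complex, von Hippel-Lindau disease, HNF-1β-related disease, ADTKD, ARPKD and NPHP. It therefore mixes dominant and recessive disease in genes that the described MLPA step does not address.

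Three things are at stake:

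1. A patient whose causal allele is a deletion may be recorded as having no mutation found.
2. Diagnostic yield would mean different things by class, since only typical ADPKD is described as tested for deletions. One stated aim is a customised pipeline for each disease subtype, so yields compared by class should rest on the same variant types.
3. In a recessive gene, a patient with a small variant on one allele and a deletion on the other may be given the wrong genotype.

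**Working it through.** **Tests described, by class** (sizes from Study participants; tests from Genetic pipeline and the Fig. 1 legend)

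| Class | Planned n | First step | After a negative panel | Large-deletion step described |
|---|---|---|---|---|
| Typical ADPKD | 650 | Panel, SNVs and indels | Long-range PCR + MLPA, then WES | Yes, tied to PKD1 |
| Atypical polycystic kidney disease | 90 | Panel, SNVs and indels | WES | None |
| Other/paediatric iCKD | 60 | Panel, SNVs and indels | WES | None |

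The sizes agree with the stated total: 650 + 90 + 60 = 800. The classes with no described deletion step hold 90 + 60 = 150 patients, and 150/800 = 18.75%. Other iCKD alone is 60/800 = 7.5%. Deletions in non-PKD genes are also uncovered among the 650.

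**Would another planned step catch them?**

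- *Visual review.* It is applied to variants in order to remove false positives. A lost exon produces no SNV or indel record to inspect.
- *WES.* It might, if copy number is called from it; the article does not say. A case that already looks solved would reach WES only through the severity or family-discordance triggers.
- *Segregation.* If both parents are tested, an apparent homozygote with one non-carrier parent is a warning sign. But a case that looks solved need not meet any of the collection triggers.

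**Illustration.** The article gives no deletion share. Let q be an assumed share of causal alleles that are large deletions, with the two alleles of a recessive patient independent, every small variant called and no deletion called.

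- Both alleles seen: (1−q)²
- One allele an unseen deletion: 2q(1−q)
- Both alleles unseen: q²
- Dominant disease, causal allele unseen: q

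| q (assumed) | Both seen | One unseen | Both unseen |
|---|---|---|---|
| 1% | 98.01% | 1.98% | 0.01% |
| 5% | 90.25% | 9.5% | 0.25% |
| 10% | 81% | 18% | 1% |
| 20% | 64% | 32% | 4% |
| 30% | 49% | 42% | 9% |

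The middle group splits. If the deletion covers the site of the small variant, only the variant base is read there and the genotype appears homozygous. Otherwise the patient appears as a single heterozygote. With f the fraction covered, false homozygosity is 2q(1−q)f, which is at most 2q(1−q). The article gives no basis for f.

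As brackets on the 60 other-iCKD patients, for q = 1%, 5%, 10%, 20%, 30%:

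- all dominant, 60q = 0.6, 3, 6, 12, 18 patients with the causal allele missed;
- all recessive, 60 × 2q(1−q) = 1.2, 5.7, 10.8, 19.2, 25.2 patients with one allele missed.

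The class is mixed, so neither bracket describes it and neither is a forecast.

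**The case against.** The strongest reply is that this argues from silence. The sentence on SNVs and indels concerns the panel reads and does not say that nothing else is called. The variant types called from WES are not given, and a journal article may leave them to the full protocol. This stands to the following extent: a reader might infer that deletions outside typical ADPKD cannot be detected, and the text does not support that. It supports only that no described step would detect them. Condensation does not explain away the rest, however. The section gives the aligner, the genome build, the depth threshold and the second-line assay for each class, and it places the deletion assay in one class. That is a stated choice.

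A reader might also infer that a small variant opposite a deletion will be misread as homozygous. That goes too far: it needs the deletion to cover the variant's site, and parental testing could expose the error. It is a risk, and 2q(1−q) is only its ceiling. Nor do false negatives and false homozygotes add up in the same patients, since an apparent homozygote counts as solved.

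Finally, a reader might infer that genotype-severity contrasts are pulled towards the null. The Genotype-phenotype correlation analysis section defines no mutation-negative comparison group and no specific severity contrast for the 60 other-iCKD patients, so that bias is not shown.

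**Conclusion.** The point holds as a gap in the described pipeline. For 150 of 800 planned patients, and for non-PKD genes in all classes, no described step would detect whole-exon or whole-gene deletions. Yield by class is then not like for like, and some deletion carriers may be recorded as negative or, in recessive genes, given the wrong zygosity or left as single heterozygotes.

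The 150 comes from the article. How many patients would be affected cannot be computed from it: every figure above that depends on q rests on an assumed deletion share, independent alleles and an all-dominant or all-recessive class. The conclusion would shrink if the full protocol already specifies copy-number calling from the panel or WES reads. The change is worth making because it serves a stated aim and uses data that the study will already have.

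**What to change.** In the Genetic pipeline section and Fig. 1:

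1. Add read-depth copy-number calling on the existing panel and WES reads, for all panel genes and all three classes, before a patient is declared mutation-negative. State which variant types are called from WES.
2. In recessive genes, check read depth at the site of each apparently homozygous finding, and across the gene for each single-heterozygous finding. Use family samples where they have already been collected.
3. Report yield by class with and without copy-number calls. If calling is not adopted, label yield outside typical ADPKD as SNV/indel only.

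This needs no new samples or sequencing. The cost is extra bioinformatics work and some false-positive copy-number calls. Their review is additional to the planned visual inspection, which is aimed at called variants and does not confirm dosage.

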## Methods/design

### Study design and settings

This is a 3-year prospective, multicenter, cohort study to elucidate genotype-phenotype associations among iCKD patients. A total of 11 medical centers from 9 tertiary hospitals in Korea will participate in this study. Seven centers will enroll and collect data from adult patients, and 4 centers will enroll pediatric patients. We established a research team, statistical analysis team, database team, sequencing and biobanking team, and genetic analysis team to perform this large nationwide project. The research team is composed of 26 clinicians and 15 clinical research coordinators from 11 medical centers. The role of the research team is to recruit eligible patients and collect clinical data. The statistical analysis team supports the calculation of sample size, distribution of enrollment according to iCKD subclasses, and statistical analysis. The database team collects clinical and genetic data from each patient and builds an electronic case report form to store and manage the dataset. The database team also performs imaging analysis quantitatively and qualitatively from nonenhanced computed tomography (CT) or sonography. The team for sequencing and biobanking is outsourced to Macrogen, Inc. to collect whole blood from each medical center and perform initial genetic analysis to produce sequencing data. The residual DNA samples will be prepared for biobanking after quantity and quality checks. Finally, the genetic analysis team is composed of bioinformaticians to interpret the results of sequencing data and to determine the pathogenicity of each variant.

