### Data collection, monitoring, and follow up

The total study scheme and annual assessment plan are depicted in Table 1. Annual laboratory assessment will be performed after enrollment for 2 years. The laboratory assessment includes the complete blood cell counts, blood urea nitrogen and serum creatinine, serum calcium and phosphorus, serum uric acid, urinalysis with microscopy, and spot urine protein to creatinine ratio. Kidney imaging will be performed every 2 years to calculate the rate of total kidney volume growth.

**Table 1 Tab1:** Study schedule

Parameter	Screen	B0	1y	2y
Informed consent	v			
Demographic information	v			
Medical history	v			
Eligibility confirmation	v			
Recent events			v	v
Medications		v	v	v
Quality of life questionnaires (EQ-5D-5L (adult), PedsQL 4.0 Generic Core Scales (pediatric))		v		
Depression assessment (PHQ-9)		v		
Nutritional assessment (mSGA)		v		
Systolic and diastolic blood pressure		v	v	v
Complete blood cell count (white blood cells, hemoglobin, platelet count, hematocrit, reticulocyte count, neutrophil count)		v	v	v
Serum calcium/phosphorus		v	v	v
Serum uric acid		v	v	v
Serum protein/albumin		v	v	v
Serum blood urea nitrogen/creatinine/estimated glomerular filtration rate		v	v	v
Plasma sodium/potassium/chloride/total carbon dioxide		v	v	v
Serum total cholesterol		v		
Highly sensitive C-reactive protein		v		
Urinalysis with microscopy		v	v	v
Spot urine protein/creatinine ratio		v	v	v
Spot urine uric acid		v		
Spot urine sodium/potassium/chloride		v		
Spot urine calcium/phosphorus		v		
Spot urine osmolality		v		
Kidney CT (adult) or abdomen sonography (pediatric)		v		

*Abbreviations*: *CT* Computed tomography, *PedsQL* Pediatric Quality of Life inventory, *PHQ-9* Patient Health Questionnaire-9, *mSGA* Modified Subjective Global Assessment

Electronic case report forms will be developed, including demographic sheets, laboratory assessments, volumetry, and genetic analysis information. The electronic case report form will be opened to the participating researchers and clinical research coordinators to fill out and modify patient information. A family tree will be drawn and stored in electronic case report form by scanning the sheet.

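### Severity helps decide who receives the testing that settles the genotype label, and that label is then analysed against severity

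*Protocol article*

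**What the plan says.** All places are in the protocol article.

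- **Uniform part (Genetic pipeline; Fig. 1 caption).** Everyone is screened with the gene panel. Patients without a pathogenic finding go on to further testing whatever their severity: long-range PCR with MLPA and then WES in typical ADPKD, and WES directly in the other classes.
- **Severity-dependent testing (Genetic pipeline).** Additional testing is also ordered "if the patients have severe renal or extrarenal phenotypes compared to other family members". WES criterion 3 applies "if the patients present with a severe phenotype and variants cannot explain the severity", and criterion 4 "if the patients show extremely different phenotypes compared to other family members".
- **Severity-dependent family sampling (Study participants).** The grounds for collecting relatives' samples include "genotype-phenotype severity is not matched, and when the extrarenal manifestation is severe". Two other grounds, an undetermined diagnosis and more than 3 affected family members, do not refer to severity.
- **Use of segregation.** Genetic pipeline says that segregation serves to define whether variants are pathogenic. The Fig. 1 caption places it last, to explain discordance between genotype and phenotype, within families, and between renal and extrarenal disease.
- **Who makes the call.** The genetic analysis team is there "to interpret the results of sequencing data and to determine the pathogenicity of each variant" (Study design and settings). The Fig. 1 caption says "All the variants will be analyzed by bioinformaticians to identify pathogenic mutations".
- **Artefact check (Genetic pipeline).** "All variants will be visualized in silico to eliminate false positives", after standard calling and a depth threshold of 8x.
- **Analysis (Genotype-phenotype correlation analysis).** Linear regression relates genotype to kidney volume and eGFR, modifier effects of multiple genes are assessed, and P < 0.05 counts as significant. Nothing limits genotype to the uniformly applied work-up.

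**The concern.** Reconciling genotype with phenotype is sensible when the aim is to diagnose one patient. It becomes circular when the reconciled label is reused as the exposure in a regression on severity. A variant that is looked for harder in severe patients will appear more often in severe patients even if it does nothing. A label that is re-examined only when it disagrees with severity can drift towards agreement.

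At stake is a central aim. Study design and settings gives genotype-phenotype association as the purpose of the cohort, and the abstract adds the search for modifying genes. Modifier variants are the most exposed. A main causal variant is usually sought in every patient. A second or off-panel variant may be sought only because the first one did not account for the severity.

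**Working it through.** **1. The chain in the text.** (a) Severity, or its mismatch with genotype, triggers WES under criteria 3–4 and family sampling. (b) WES can add variants, and segregation helps define pathogenicity. (c) The resulting genotype is related to kidney volume and eGFR. Each link is written down. No sentence breaks the chain by restricting the label used in (c).

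**2. Which labels are exposed.** Panel-negative patients reach WES regardless of severity, so for them the severity rules add little. Criteria 3–4 add WES mainly for patients who already have a panel finding. The exposed labels are therefore second, ambiguous, off-panel and modifier variants, and calls that turn on segregation in mismatch-triggered families.

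**3. Illustration of size.** The plan gives no figure to reproduce. From the documents come n = 650 (typical ADPKD) or 800 (650 + 90 + 60 = 800) and alpha = 0.05, taken as two-sided. The rest is assumed:
- severity is standard normal and unrelated to true carrier status;
- carrier share c = 5–20%;
- ordinary testing finds a share b of carriers;
- the most severe 20% get extra testing that finds 90% of the carriers missed;
- patients with no finding are coded as non-carriers.

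Bias in closed form. The 80th percentile of the standard normal is 0.842, with density 0.280.
- Share of carriers labelled: L = b + 0.2 × 0.9 × (1 − b).
- Mean severity of those labelled: m = 0.280 × 0.9 × (1 − b) / L.
- Labelled minus unlabelled: d = m / (1 − cL).

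For b = 0.5: L = 0.5 + 0.09 = 0.59 and m = 0.126 / 0.59 = 0.214. Then d = 0.214 / (1 − 0.0295) = 0.22 SD at c = 5%, and 0.214 / (1 − 0.118) = 0.24 SD at c = 20%.

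Simulation (2000 replicates per setting, linear regression of severity on the label; ranges over n and c):

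| Ordinary testing finds | False-positive rate | Mean bias |
|---|---|---|
| 80%, no severity-triggered testing | 4.7–5.7% | about 0 SD |
| 95%, plus triggered testing | 4.7–6.0% | 0.01–0.02 SD |
| 80%, plus triggered testing | 6.1–13.6% | 0.06–0.08 SD |
| 50%, plus triggered testing | 17–60% | 0.22–0.24 SD |
| 0%, plus triggered testing | 92–100% | about 1.4 SD |

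The closed form agrees with the simulated bias at b = 0.5. At b = 0 it gives m = 0.252 / 0.18 = 1.40.

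**4. Reading the table.** The first row also covers a visual check that drops 20% of true variants without regard to severity: it costs carriers but creates no bias. The last row is an extreme, because panel-negative patients get WES anyway. If 20% of carriers of an off-panel variant were found that way (an assumption), then L = 0.2 + 0.18 × 0.8 = 0.344 and m = 0.252 × 0.8 / 0.344 = 0.586. That gives d of about 0.60 SD (c = 5%) to 0.63 SD (c = 20%).

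**5. Direction.** The simulation lets the extra work only add labels, and only in severe patients. Criterion 4 and the mismatch rule can also pick out unusually mild patients, and segregation can remove a label as well as confirm one. The sign of the net bias is therefore not fixed by the text.

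**The case against.** The strongest reply is that every stated use of severity decides who is tested or sampled further, and none decides how a variant is called. Much of this stands.

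A reader might infer that the genetic analysis team weighs severity when it calls a variant pathogenic, or discards borderline calls by eye more readily in mild patients. The documents do not support that:
- The visual check is an artefact filter, and severity is not mentioned there.
- Criterion 3 is a rule for ordering WES. The text does not say who applies it.
- Study design and settings separates the clinicians who collect clinical data from the bioinformaticians who interpret sequences.
- The case report form puts both kinds of data in one place ("Electronic case report forms will be developed, including demographic sheets, laboratory assessments, volumetry, and genetic analysis information"). It is opened to participating researchers and coordinators, and the genetic analysis team is not named. Shared storage shows that access is possible, not that it is used.

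A missing classification standard, masking rule or read-review criterion is detail that an article commonly leaves to the full protocol, so its absence is no finding.

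One might also try to size the problem from the roughly 20% of typical ADPKD patients without a causative mutation in the Background. That figure comes from an earlier study sequencing *PKD1* and *PKD2* only. It counts patients with no causative finding, not patients with an ambiguous variant, and this study adds a wider panel, long-range PCR/MLPA and WES.

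The reply does not remove the point. Selective testing is enough to make a label depend on severity, and segregation carries the selection into the pathogenicity call itself.

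**Conclusion.** The point holds in a limited form. As written, the workflow lets the final genotype label depend on severity through WES criteria 3–4 and mismatch-triggered family sampling, and the planned regression does not exclude labels obtained that way.

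The size depends on how many labels change through these steps, which the documents do not say. The bias is probably small for clear causal variants that the panel or long-range PCR/MLPA finds in nearly everyone. It is potentially large for ambiguous, WES-only and modifier variants. The simulated rates rest on assumed carrier shares, detection rates and a 20% trigger group, and on coding untested patients as non-carriers. They show that the problem grows with the gap in detection. They do not predict this study's error rate or the sign of its bias.

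This is a worthwhile, inexpensive improvement to the analysis. It does not show that the team's variant calling is biased, and it is no objection to using severity to guide further diagnostic testing.

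**What to change.** For the genotype-severity and modifier analyses:

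1. Take variants from the work-up that applies regardless of severity: the panel for all, then long-range PCR/MLPA (typical ADPKD) and WES for negative results.
2. Classify them without sight of kidney volume, eGFR, Mayo class, CKD stage or the reason for extra testing.
3. Lock this list before linking it to phenotype data.
4. Keep variants found or reclassified only through severity-triggered WES or severity-triggered segregation as a separate diagnostic label, and report them descriptively.

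No extra tests or patients are needed, and individual diagnosis is unaffected. The cost is a short delay for the lock, two labels to maintain, and somewhat fewer variants in the regression, felt mostly in the modifier analysis.
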